### Labour pain

The pain of labour is a central part of women's experience of childbirth and is a constant feature of antenatal discussion groups [11]. Most women giving birth use some methods of pain relief (pharmacologic and/or non-pharmacologic) during labour. In Australia 92% of primiparas and 71% of multiparas use some analgesic agents for labour analgesia [12]. Significantly, there have been more clinical trials of pharmacological pain relief during labour and childbirth than of any other intervention in the perinatal field [13].

However satisfaction with childbirth is not necessarily contingent upon the absence of pain [14]. Many women are willing to experience pain in childbirth but do not want pain to overwhelm them. The Royal College of Obstetrics and Gynaecology (RCOG) makes the following evidence-based recommendations [15]:

• Continuous caregiver support for a single individual should be available to women in labour

• Midwives must involve women in decisions about analgesia and recognise the value of promoting personal control

• Maternity services should ensure access to written and verbal information on pain relief and should support women in their choices for pain relief

• Maternity services should respect women's wishes to have some control over their pain relief

• Improved public information and data on pain and analgesia

In Australia over 250,000 women give birth annually and the increasing use of epidural analgesia means some 75,000 women have an epidural in labour each year [16]. Among primiparas in NSW, the epidural rate increased from 25% in 1990 to 42% in 2000, but was as high as 74% in hospitals with greater availability of epidurals [12]. Other pharmacologic methods of pain relief for primiparas include 36% opioids and 55% nitrous oxide [12].

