### 2. Hypotheses

The primary study hypotheses are:

Use of the Pain Relief for Labour Decision Aid by women expecting their first baby:

1. Reduces decisional conflict (uncertainty about the course of action)

2. Increases knowledge of labour analgesia

3. Increases satisfaction with their decision making

4. Reduces anxiety.

The secondary hypotheses of the study are:

Use of the Pain Relief for Labour Decision Aid by women expecting their first baby will not influence:

1. The type of analgesia women use for labour

2. Maternal and infant outcomes.

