### 11 statistical issues

#### Sample size

The planned sample size is 600 women, with approximately 200 women to be recruited to each arm of the trial. Based on data for 2001 from the tertiary obstetric hospital where the study will be conducted, about 1500 primiparous women give birth to singleton infants after 36 weeks gestation and 92% use some form of analgesia. We anticipate that at least 50% of women will be both eligible and willing to participate.

The sample size calculations for the trial (significance 0.05, power 0.8) are based on the mean difference in the decisional conflict scale between any two arms of the trial. The effect of decision aids on this scale is documented and effect size data are available [1]. Meta-analysis of four randomised controlled trials comparing a decision aid to a pamphlet and that report a mean difference in decisional conflict gives a pooled mean difference of -4.35, 95%CI -6.8, -1.9 (on a scale ranging from 0 lowest to 100 highest decisional conflict; median standard deviation 13.0) [35-38]. Assuming a mean difference of -4.35 and standard deviation 13.0, we will need about 141 women in each arm of the trial to demonstrate a difference in decisional conflict.

Approximately 20% of primiparous women have a caesarean section (6% before labour and 14% after labour has commenced) [12]. Some of these women will lose their options for analgesia, although some may have extensive use of analgesic agents prior to caesarean section (CS). We plan to conduct an a priori sub-group analysis that excludes women who lose their options for analgesia (defined as a CS planned after randomisation, an emergency CS within 1 hour of arriving in labour or those who receive a therapeutic epidural) as these women may have different satisfaction, anxiety and decisional conflict outcomes. We will inflate the sample size estimate by 20% (from 141 to 169) to ensure sufficient power in the sub-group analyses. A further inflation of 15% for loss to follow-up, gives the final sample size of at least 195 women in each arm of the trial.

If there are no significant differences in outcome for the two decision aid groups (with or without the audio-component), the decision aid groups will be pooled giving two women with the intervention for each woman in the pamphlet group thereby increasing the power to detect differences between the decision aid and the pamphlet.

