#### Data analysis

Analyses will be by intention to treat, including withdrawals and losses to follow-up firstly of all women randomised and then excluding women who lose their options for analgesia. Study groups will be compared in terms of baseline characteristics. As this is a randomised trial, we would anticipate minimal differences in baseline characteristics. If however, important differences are found, these potential confounders will be adjusted for in the analysis of outcomes. For the primary outcomes, the mean score for each measure for each group will be compared using t-tests. If adjustment for confounders is needed a multiple linear regression model will be used. The secondary outcomes will be compared using chi-squared tests of significance for categorical data and t-tests for continuous data. If adjustment for confounding is necessary logistic regression and multiple linear regression will be used respectively.

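### The secondary hypotheses claim no influence, but the planned tests of difference cannot support that claim; they should be restated as estimation with confidence intervals

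*Protocol article*

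**What the plan says.** Under 2. Hypotheses, the protocol article lists two secondary hypotheses, introduced by "Use of the Pain Relief for Labour Decision Aid by women expecting their first baby will not influence". The first concerns the type of labour analgesia, the second maternal and infant outcomes.

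Under Data analysis, the method for these outcomes is fixed: "The secondary outcomes will be compared using chi-squared tests of significance for categorical data and t-tests for continuous data". Logistic or linear regression follows if confounders need adjustment.

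Under Sample size, one outcome drives the calculation: "The sample size calculations for the trial (significance 0.05, power 0.8) are based on the mean difference in the decisional conflict scale". The same section plans about 200 women per arm. It also pools the two decision aid arms if they do not differ significantly, which gives about 400 v 200.

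For event rates, the Labour pain section reports that among primiparas in New South Wales "the epidural rate increased from 25% in 1990 to 42% in 2000, but was as high as 74% in hospitals" with greater availability. It also gives 36% for opioids and 55% for nitrous oxide.

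**The concern.** A test whose null hypothesis is no difference can contradict a hypothesis of no influence but cannot support it. The less precise the comparison, the more likely that hypothesis is to go unchallenged. The article states the no-effect hypotheses and the difference tests together, so the mismatch is in its own text and is not a detail deferred to an analysis plan.

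The matter bears on this trial's message. The article stresses several times that the aid is non-directive and is not meant to raise or lower intervention rates. It also lists adverse consequences of epidural analgesia, such as prolonged labour and instrumental delivery. If a non-significant comparison were taken as confirming the secondary hypotheses, a real shift in epidural use could be reported as absent.

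**Working it through.** **1. The plan's own figure.** The inputs are "significance 0.05, power 0.8" and, from the same section, "Assuming a mean difference of -4.35 and standard deviation 13.0, we will need about 141 women in each arm". With a two-sided test (sidedness is not stated):

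n = 2 × [(1.960 + 0.842) × 13.0 / 4.35]² = 140.2, rounded up to 141 per arm.

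The inflations are "We will inflate the sample size estimate by 20% (from 141 to 169") and "A further inflation of 15% for loss to follow-up, gives the final sample size of at least 195 women in each arm". These reproduce: 141 × 1.20 = 169.2 and 169 × 1.15 = 194.4, rounded up to 195. The calculation is sound for decisional conflict. No secondary outcome enters it.

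**2. Precision for analgesia type.** The rates come from Labour pain and Sample size, the arm sizes from Sample size. It is an assumption that these rates apply to the trial population, so the epidural range of 42% to 74% is carried through. At an observed difference of zero:

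SE = √[p(1 − p)(1/n₁ + 1/n₂)], 95% half-width = 1.96 × SE.

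Example at p = 0.42: √(0.2436 × 0.0100) = 4.94 points, half-width 9.7 (200 v 200); √(0.2436 × 0.0075) = 4.27 points, half-width 8.4 (400 v 200).

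| Outcome (rate) | 200 v 200 | 400 v 200 |
|---|---|---|
| Epidural (42%) | 9.7 | 8.4 |
| Epidural (74%) | 8.6 | 7.45 |
| Opioids (36%) | 9.4 | 8.1 |
| Nitrous oxide (55%) | 9.8 | 8.4 |
| Caesarean (20%) | 7.8 | 6.8 |
| Any analgesia (92%) | 5.3 | 4.6 |

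The entries are percentage points. A non-significant result with a non-zero observed difference leaves larger shifts open on one side.

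**3. How often a true 10-point shift in epidural use would be non-significant.**

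Power = Φ[(d − 1.96 × SE₀)/SE₁], where SE₀ uses the pooled proportion and SE₁ the two separate proportions.

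Example, 42% v 52% at 200 v 200: SE₀ = 0.04991 and SE₁ = 0.04966, so (0.10 − 0.0978)/0.04966 = 0.04. Power is 0.52, so 48% of trials miss the shift.

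| Pamphlet → aid | Missed, 200 v 200 | Missed, 400 v 200 |
|---|---|---|
| 42% → 52% | 48% | 36% |
| 42% → 32% | 46% | 33% |
| 74% → 64% | 42% | 30% |
| 74% → 84% | 31% | 18% |

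**4. What a formal equivalence test could deliver.** The document gives no margin, so ±10 and ±15 points are illustrations. With two one-sided 5% tests and a true difference of zero:

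Power = 2Φ(margin/SE − 1.645) − 1.

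- ±10 points at 42% use: 30% (200 v 200), 51% (400 v 200). At 74% use, pooled: 68%.
- ±15 points at 42% use: 84% (200 v 200), 94% (400 v 200).

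**5. Infant outcomes.** For continuous measures such as birthweight, the difference detectable with 80% power is 2.80 × √(2/200) = 0.28 SD (200 v 200) or 2.80 × √(1/200 + 1/400) = 0.24 SD (400 v 200). For perinatal death, zero events among 400 aid women would leave an exact upper 95% limit of 1 − 0.025^(1/400) = 0.92%.

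**The case against.** The strongest reply is that the article never says a p-value above 0.05 will be taken to show no influence. A reader might infer that rule from the hypotheses and tests together, but it is not stated. The Data analysis section says only that the outcomes will be compared. The abstract and the Secondary outcomes section speak of monitoring, recording and comparing, and the hypotheses can be read as an expectation. This stands, and it confines the point to the mismatch between the worded hypothesis and the named test. The mismatch remains, because these tests offer no other route to supporting a no-influence hypothesis.

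A second tempting reading is that shifts of 8–10 points go unexcluded for every secondary outcome. They do not. That range suits the main analgesia methods at a zero observed difference; the intervals are narrower for caesarean section and for any analgesia, and the pooled epidural figure at 74% is below 8. The higher rate may also be the relevant one, since the Setting section describes round-the-clock epidurals from dedicated staff. Miss rates are lower there, so the full range has to be shown.

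A third is that the trial carries almost no information on infant outcomes. That is wrong for birthweight and gestational age, where a quarter of a standard deviation is within reach. It is fair for perinatal death. The article gives no neonatal intensive care admission rate, so nothing can be said about that outcome.

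Finally, sizing a trial on one primary outcome is ordinary practice, and an article may leave margins and interval reporting to a fuller document. Neither is held against the plan here.

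**Conclusion.** The point holds in limited form. The secondary hypotheses assert no influence, the named analysis tests only for difference, and the trial was not sized for these outcomes, so a non-significant result cannot support the hypotheses as worded. For epidural use, the main case, a result of exactly zero difference would still leave shifts of about 7.5 to 9.7 points unexcluded, and a true 10-point shift would be missed in roughly a fifth to a half of trials.

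These figures assume full arms of 200, epidural use between the cited 42% and 74%, and two-sided 5% tests. The planned analysis that excludes women who lose their analgesia options would be less precise. The consequence is confined to what may be concluded about secondary outcomes; the primary comparisons and the sample size for decisional conflict are not touched.

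**What to change.** Restate both secondary hypotheses as estimation of the aid-minus-pamphlet difference. Report risk differences with 95% confidence intervals for each main analgesia method and for categorical maternal and infant outcomes, and mean differences with 95% intervals for continuous ones. Word a non-significant result along these lines: *no difference shown; shifts of up to X points not excluded*. Report perinatal deaths descriptively with an interval, and make no claim of no influence for them.

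If the sponsor wants to claim no material influence on epidural use, it should fix a margin before data are seen and make the claim only if the interval lies wholly inside it. This is offered as an option and not as the main remedy. At 42% use a ±10-point margin is underpowered even with pooling, and ±15 points is close to the 17-point rise (42 − 25) that the article reports over a decade, so meeting it would say little.

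The cost is wording in the hypotheses and analysis sections; no extra women or data are needed. The downside is a weaker statement about the aid's neutrality.

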### 3. Study design

We will conduct a randomised trial with the following study groups to assess the impact of the decision aid:

Group 1: The pamphlet, "Pain relief during childbirth – A guide for women" [29]

Group 2: Decision aid with an audio-component

Group 3: Decision aid without an audio-component

### 4. Setting

An Australian tertiary obstetric hospital with a full range of non-drug and anaesthetic options for pain relief in labour. Epidurals are available 24 hours a day from anaesthetic staff designated to labour ward. All forms of antenatal care (clinic, birth centre, private, shared care with a family physician) will be included in the study.

### 5. Participants/eligibility criteria

Primiparous women in late pregnancy (≥36 weeks gestation) who are expecting to have a vaginal birth of a single infant will be eligible for the study. Primiparous women were selected because previous pregnancies have a strong impact on decision making and analgesia use in labour [14,16]. Exclusions include women who will not have any choice about analgesia, for example planned caesarean section (eg breech, placenta praevia, HIV), planned epidural (eg symptomatic heart disease), contraindications to analgesia (e.g drug sensitivities, anticoagulants, thrombocytopaenia). The decision aid was produced in English and designed to be simple and accessible for women with low levels of literacy.

### 6. Procedures, recruitment, randomisation and collection of baseline data

The study procedure draws on the usual schedule of weekly antenatal visits in late pregnancy (Figure 1). We plan a pragmatic approach to assess the decision aid under the conditions most likely to be applied in practice. A research nurse will ask eligible women to participate, explain the trial and obtain informed consent, collect baseline data and randomly allocate women (using telephone randomisation) to one of the study groups. This is only a minor deviation from current practice. As women of child-bearing age are known to be very mobile, participants will be asked to provide alternate contact details (eg friend or relative) to enhance subsequent follow-up. Private obstetricians will be asked to offer participation in the study to their patients. Those interested will be requested to come to the antenatal clinic for recruitment and randomisation. The private obstetrician will provide standard care. Flyers and posters will be prepared to inform women of the study and will be distributed through family physicians and obstetricians as well as the clinics.

**Figure 1 F1:**
[figure not shown]
Schema of Pain Relief for Labour Decision Aid trial

Brief baseline data will be collected to assess comparability of the study groups. The baseline assessment will include age, brief socio-demographic data, highest level of education achieved, anxiety as assessed by the state component of the short Spielberger anxiety scale [30], and information sources about labour analgesia.

### 7 Intervention

The aim of the decision aid is to assist preference elicitation, and not to influence the direction of the decision taken. Women in each study group will be given the opportunity to review the intervention they are allocated (decision aid or pamphlet) while in the antenatal clinic and/or to take home, which ever is most convenient. Many women will also want to discuss their preferences with their partner. At the next antenatal visit, women will be contacted by the research nurse to discuss the information materials and any questions they may have had.

### 8 Follow-up

#### i) First follow-up questionnaire

All participants will be given a follow-up questionnaire prior to their next antenatal consultation. (See Outcome Measure details below).

#### ii) Midwife questionnaire

After a study participant delivers, the midwife who provided the labour care will complete a brief questionnaire to assess the impact of the decision aid on the management of labour analgesia. Information will also be collected on caregiver support in labour, birthplace (delivery suite or birth centre), use of non-drug analgesic options and stage of labour at admission.

#### iii) Second follow-up questionnaire

At 12–16 weeks postpartum all participants will be mailed a second follow-up questionnaire. This will assess women's satisfaction with the decisions made and the decision-making processes. (See Outcome Measures below). Questionnaires will be mailed with reply paid envelopes, with up to two reminder telephone prompts to non-responders.

#### iv) Qualitative follow-up

We will conduct in-depth interviews to explore the impact of the decision aid on women's experiences in labour and childbirth. A sub-sample of 30 women will be purposively selected, to reflect heterogeneity of experience of labour. The interviews will provide an understanding of the complexities of analgesic preferences, management, expectations, satisfaction, and psychological health following delivery. This data will enable examination of unpredicted and subtle effects of the decision aid on psychosocial outcomes that may not be captured using quantitative methods. Interviews will be face-to-face and conducted in women's homes or at a clinic, according to participants' preferences. Interviews will be recorded and transcribed. Data will be analysed using thematic analysis.

### 9. Blinding and contamination

As with many obstetric interventions blinding is virtually impossible. The main outcomes of this study are self-reported and the women are clearly not blinded to their treatment allocation. However, we will institute a number of measures aimed at keeping antenatal staff blind to the treatment allocation and preventing contamination of the control group:

• Women will review the decision aid with the research nurse and complete the first questionnaire (primary outcome measures) prior to their next antenatal consultation

• Usual antenatal care providers will be blinded to the exact content and format of the decision aid

• Regular in-service (educational training) for the antenatal care providers to explain the trial protocol and to make clear the potential effect of unmasking or contamination.

• Monitoring decision aid distribution and keeping them locked up and only accessible by the research nurse

• Asking participants not to reveal their treatment allocation, or share their decision aid material with antenatal staff or other women. If participants do not want to keep their decision aid they will be asked to return it.

### 10 outcome measures

#### Primary outcomes

The primary outcomes of this study will be:

*Decisional conflict *(uncertainty about which preference to choose) will be assessed by the Decisional Conflict Scale which has established reliability, good psychometric properties and is short (16 items) [31]. It has been used to evaluate a range of decision aids [1].

*Measures of knowledge and realistic expectations *about labour analgesia options and the benefits and risks of these options will be specific to this project. Thus we will need to develop, and test these measures as part of the project.

*Anxiety *will be measured by the state component of the short Spielberger anxiety scale which has been extensively used and validated [30,32]. We do not anticipate the decision aid will increase women's anxiety but it is important to document any changes in anxiety associated with the decision aid.

*Satisfaction *with analgesia decisions will be assessed using the Satisfaction with Decision Scale – a very brief six item scale with high reliability was developed specifically to assess satisfaction with health care decisions [33].

Satisfaction with the decision and anxiety will be measured again at 12–16 weeks postpartum. This interval was chosen to avoid the potential bias arising from questioning women still in the hospital who may feel a disloyalty to their caregivers by a critical appraisal and whose opinions have been shown to be more positive and short-lived than those obtained further out from the birth itself [34]. At that time we will also ask about exposure to the decision aid (to assess contamination), support during labour and use of pain relief methods prior to hospital admission. These issues will be further explored in the sample selected for in-depth interview.

#### Secondary outcomes

##### Service utilisation outcomes

The aim of the decision aid is to assist preference elicitation, and not to influence the direction of the decisions taken. Nevertheless, it is important to collect service utilisation and pregnancy outcome data so we will record and compare the pain relief methods used by women in all arms of the study, as well as recording and comparing rates of pregnancy complications and perinatal outcomes. The latter will be obtained (with informed consent) from the existing computerised obstetric database and include: medical or obstetric complications, induction or augmentation of labour, mode of delivery (vaginal, emergency or planned CS), enrolment to delivery interval, gestational age, birthweight, Apgar scores, perinatal deaths, Neonatal Intensive Care Unit admission and length of stay.

### 11 statistical issues

#### Sample size

The planned sample size is 600 women, with approximately 200 women to be recruited to each arm of the trial. Based on data for 2001 from the tertiary obstetric hospital where the study will be conducted, about 1500 primiparous women give birth to singleton infants after 36 weeks gestation and 92% use some form of analgesia. We anticipate that at least 50% of women will be both eligible and willing to participate.

The sample size calculations for the trial (significance 0.05, power 0.8) are based on the mean difference in the decisional conflict scale between any two arms of the trial. The effect of decision aids on this scale is documented and effect size data are available [1]. Meta-analysis of four randomised controlled trials comparing a decision aid to a pamphlet and that report a mean difference in decisional conflict gives a pooled mean difference of -4.35, 95%CI -6.8, -1.9 (on a scale ranging from 0 lowest to 100 highest decisional conflict; median standard deviation 13.0) [35-38]. Assuming a mean difference of -4.35 and standard deviation 13.0, we will need about 141 women in each arm of the trial to demonstrate a difference in decisional conflict.

Approximately 20% of primiparous women have a caesarean section (6% before labour and 14% after labour has commenced) [12]. Some of these women will lose their options for analgesia, although some may have extensive use of analgesic agents prior to caesarean section (CS). We plan to conduct an a priori sub-group analysis that excludes women who lose their options for analgesia (defined as a CS planned after randomisation, an emergency CS within 1 hour of arriving in labour or those who receive a therapeutic epidural) as these women may have different satisfaction, anxiety and decisional conflict outcomes. We will inflate the sample size estimate by 20% (from 141 to 169) to ensure sufficient power in the sub-group analyses. A further inflation of 15% for loss to follow-up, gives the final sample size of at least 195 women in each arm of the trial.

If there are no significant differences in outcome for the two decision aid groups (with or without the audio-component), the decision aid groups will be pooled giving two women with the intervention for each woman in the pamphlet group thereby increasing the power to detect differences between the decision aid and the pamphlet.

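### The 20% inflation is not matched to the women the exclusion analysis drops, so its power assurance is not demonstrated; nor should that exclusion be applied to decisional conflict

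*Protocol article*

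**What the plan says.** The Sample size section sizes the trial on decisional conflict: "The sample size calculations for the trial (significance 0.05, power 0.8) are based on the mean difference in the decisional conflict scale". The base requirement follows: "Assuming a mean difference of -4.35 and standard deviation 13.0, we will need about 141 women in each arm of the trial".

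The section then gives a caesarean rate, "Approximately 20% of primiparous women have a caesarean section (6% before labour and 14% after labour has commenced", and remarks that only some of these women lose their analgesic options. The women to be left out of a pre-specified subgroup analysis are "defined as a CS planned after randomisation, an emergency CS within 1 hour of arriving in labour or those who receive a therapeutic epidural". The reason given is that their satisfaction, anxiety and decisional conflict may differ. The allowance for this is: "We will inflate the sample size estimate by 20% (from 141 to 169) to ensure sufficient power in the sub-group analyses". A further 15% for loss to follow-up brings the figure to at least 195 per arm, with about 200 planned.

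The Data analysis section applies the exclusion generally: all randomised women are analysed first, and then the set without the excluded women. It makes no distinction between outcomes.

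On timing, the section on blinding and contamination has women "complete the first questionnaire (primary outcome measures) prior to their next antenatal consultation". Under Primary outcomes, only satisfaction and anxiety are named as repeated at 12–16 weeks postpartum.

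**The concern.** There are two separate problems.

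**The inflation figure.** The text does not say outright where the 20% comes from, but it equals the caesarean rate given just before it, and no other source is offered. That rate describes a different group from the one excluded. No expected share is given for any of the three exclusion criteria, and therapeutic epidural is not defined. The step accounts for about 32 women per arm: without it the plan's own method gives 141 × 1.15 = 162.15, so 163, against 195. It also carries an explicit promise of sufficient power.

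**The outcome it is applied to.** The exclusion depends largely on what happens in labour, whereas decisional conflict is recorded before labour. Dropping women from that analysis because of later events discards valid data, and does so on a post-randomisation basis. It also conflicts with the stated rationale, since a labour event cannot have altered an answer already given.

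**Working it through.** **1. Reproduce the plan's figures.** Inputs from the Sample size section: difference 4.35, SD 13.0, significance 0.05 (two-sided reproduces the result), power 0.80, equal arms.

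- n per arm = 2 × [13.0 × (1.960 + 0.842) / 4.35]² = 140.2, so 141.
- 141 × 1.20 = 169.2, stated as 169.
- 169 × 1.15 = 194.35, stated as at least 195.

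The stated chain reproduces. Each step uses n × (1+d).

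**2. Compare the 20% with the exclusion definition.**

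| Part of the caesarean rate, or criterion | In the 20%? | In the excluded group? |
|---|---|---|
| Before labour (6%), already planned at entry | Yes | No: ineligible under section 5, "planned caesarean section (eg breech, placenta praevia, HIV" |
| Before labour, planned after randomisation | Yes | Yes, share not given |
| After labour began (14%), within 1 hour of arrival | Yes | Yes, share not given |
| After labour began, later than 1 hour | Yes | Not by the caesarean criterion |
| Therapeutic epidural without caesarean | No | Yes, share not given |

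For the two caesarean criteria, 20% is an upper limit. For the epidural criterion it allows nothing. The direction of the net error cannot be determined from the document.

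**3. Power of the exclusion analysis.** With N per arm, 15% loss and excluded share e, the evaluable number is n = N × 0.85 × (1−e), and power = Φ(4.35 / (13.0 × √(2/n)) − 1.960).

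At the plan's own 20%:

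- N = 195: n = 195 × 0.85 × 0.80 = 132.6; standard error 1.597; 4.35/1.597 − 1.960 = 0.765; power 0.778.
- N = 200: n = 200 × 0.85 × 0.80 = 136.0; standard error 1.576; 4.35/1.576 − 1.960 = 0.799; power 0.788.

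The other shares below are assumptions, because the document gives none.

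| Excluded share | n (195 per arm) | Power | n (200 per arm) | Power |
|---|---|---|---|---|
| 10% | 149.2 | 0.824 | 153.0 | 0.833 |
| 14% | 142.5 | 0.807 | 146.2 | 0.816 |
| 20% | 132.6 | 0.778 | 136.0 | 0.788 |
| 30% | 116.0 | 0.722 | 119.0 | 0.733 |

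The largest share that still leaves 141 women per arm is 1 − 141/165.75 = 14.9% for 195 per arm and 1 − 141/170 = 17.1% for 200.

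**4. Why it falls short at exactly 20%.** To keep 141 after losing a fraction d, one divides by (1−d): 141 / 0.80 / 0.85 = 207.4, so 208 per arm. Multiplying by 1.20 and 1.15 gives 195.

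**5. Timing.** Decisional conflict belongs to the first questionnaire, due before the next antenatal consultation, and section 6 describes visits in late pregnancy as weekly. Emergency caesarean on arrival in labour and epidural in labour both come afterwards. The postpartum questionnaire repeats satisfaction and anxiety, so those are the scores that the events could affect.

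**The case against.** The strongest defence of the 20% is that it was a cautious ceiling. The section itself says that only some caesarean women lose their options, and the ineligible planned caesareans and the one-hour limit both make the true share smaller. This stands for the two caesarean criteria, so it would be wrong to say the figure has no basis. It does not answer the epidural criterion, for which no allowance is made.

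A reader might infer that the analysis is badly underpowered, since the Labour pain section reports that "the epidural rate increased from 25% in 1990 to 42% in 2000" among primiparas in NSW. Were 42% excluded, power at 195 per arm would be about 64%. The document does not support that reading. The criterion concerns women who lose their options, and a woman who chooses an epidural has used one. Section 5 lists planned epidural, with heart disease as its example, among women without a choice, which suggests that therapeutic means medically indicated. No figure in the document puts such epidurals near that level.

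The consequence is also limited. The analysis of all randomised women comes first and has about 86% power at 195 per arm after 15% loss. If the two decision aid arms are pooled, as the plan allows, the comparison with the pamphlet at 20% excluded (132.6 against 265.2 women) has about 88% power.

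Finally, a caesarean might be planned after randomisation but before the first questionnaire. That is conceded: the timing argument covers events in labour, not every excluded woman.

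**Conclusion.** The point holds in limited form. The 20% evidently comes from the overall caesarean rate and does not match the exclusion definition, so sufficient power is asserted but not demonstrated. At the plan's own 20% and 15%, pairwise power is about 78 to 79% against the stated 80%, a shortfall of one to two percentage points. It reaches 80% only if no more than about 15% (195 per arm) or 17% (200 per arm) are excluded. A serious deficit is not shown.

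The second part does not depend on these figures: an exclusion triggered by labour events has no place in the analysis of decisional conflict or of other measures on the antenatal questionnaire.

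The power figures assume a difference of 4.35, SD 13.0, a two-sided test and the full 15% loss applying to the outcome analysed. With no loss at all, 195 per arm and 20% excluded would leave 156 women and 84% power. The analysis of all randomised women is unaffected.

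**What to change.** - In the Sample size and Data analysis sections, analyse decisional conflict, knowledge and the other first-questionnaire measures in all randomised women only.
- Keep the exclusion as a supportive analysis of satisfaction and anxiety at 12–16 weeks.
- State what therapeutic epidural covers for the purpose of this analysis.
- Replace the assurance of sufficient power with the power at the expected excluded share among eligible women, allowing for both losses with N/(1−d). If that share cannot be obtained, give about 78% at 20% excluded (195 per arm).
- Say that this power refers to a difference of 4.35/13.0 = 0.33 SD. The document gives no effect size for the postpartum scores, so it carries over to them only for a difference of that standardised size.

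The cost is revised wording, an estimate of the excluded share if the hospital's data can supply one, and a slightly less favourable stated power. No extra women are needed.
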